#### Management of dropout cases

For dropout cases, researchers should actively take measures to complete the last laboratory test as far as possible in order to analyze its efficacy and safety. For all dropout cases, the test conclusion form and reason for dropout shall be filled in the case report form.

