**Fig. 1 Fig1:**
[figure not shown]
The flow chart of the trial

The visual analogue scale (VAS) scores, symptoms, and physical scores are obtained for pre- and post-treatment periods. The concentrations of SP and β-Ep in peripheral plasma will also be detected, and demand for temporary analgesics and side effects of the patients are recorded daily. As the final stage, after 6 months, the participants are to be followed up for postherpetic neuralgia, 6 months after treatment (Fig. 2).

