### Dropout

#### Case dropout

Subjects experienced other comorbidities, complications, or special physiological changes during the trial. They are classified as not suitable to continue the trial.During the trial, serious adverse events and important adverse events occur in the subjects, so they are not suitable to continue the trial, and investigators decide to withdraw.Subjects have poor compliance. Medication compliance is calculated using the tablet counting method. Medication compliance = dose taken/prescription dose × 100%; medication compliance < 80% or missed fire needle plus cupping treatment ≥ 1 time is defined as poor compliance.Violation of the test plan. Subjects change or add drugs other than the study protocol, and received other treatments other than the study protocol during the trial period.The subject withdrew out by himself.Lost to follow-up at the final stage.

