#### Follow-up

To evaluate the incidence of postherpetic neuralgia symptom, a follow-up call is designed and recorded 6 months later posted after the end of the 1-week treatment. (Table 2).

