### Outcomes

#### Primary outcome

The primary outcome has been the changes in pain intensity pre- and post-treatment (VAS 0–100 mm, where 0 = *painless* and 100 = *maximum imaginable pain*).

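### The dropout rules do not separate stopping treatment from leaving the trial, and name a laboratory test rather than the VAS as what to secure afterwards

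*Protocol article*

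**What the plan says.** The Case dropout section lists the ways in which a patient becomes a dropout.

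- Comorbidities, complications or special physiological changes: "They are classified as not suitable to continue the trial".
- Serious or important adverse events: "so they are not suitable to continue the trial, and investigators decide to withdraw".
- Poor compliance: "medication compliance < 80% or missed fire needle plus cupping treatment ≥ 1 time is defined as poor compliance".
- Departure from the plan: "Subjects change or add drugs other than the study protocol, and received other treatments other than the study protocol during the trial period".
- Withdrawal by the patient, and loss at the final follow-up, are separate entries.

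The next section, Management of dropout cases, says what to do with all of them: "researchers should actively take measures to complete the last laboratory test as far as possible in order to analyze its efficacy and safety". It also asks for a conclusion form and the reason for dropout in the case report form. It names no other data.

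Under Primary outcome: "The primary outcome has been the changes in pain intensity pre- and post-treatment", on a 0–100 mm VAS. On timing, the study design text says: "The visual analogue scale (VAS) scores, symptoms, and physical scores are obtained for pre- and post-treatment periods". The only laboratory measurements listed under Secondary outcomes are substance P and beta-endorphin by immunoassay. Under Statistical analysis, missing main efficacy values are filled by last observation carried forward (LOCF), other efficacy values are not, and both a full analysis set (FAS) and a per-protocol set are analysed.

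**The concern.** The instruction on dropouts is meant to preserve material for judging efficacy, yet it does not name the measure on which efficacy is judged. Most of the listed reasons (adverse event, complication, non-adherence, other treatment) do not mean that the patient has refused further contact. In a one-week trial the end-of-week reading is at most days away and takes one question.

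If staff pursue only what is named, the primary outcome goes missing in patients who could have supplied it. These patients are not a random sample. They are defined by side effects, adherence and use of other treatment, and the three open arms differ in all of these. The FAS comparison would then rest partly on carried-forward values that could have been observed ones.

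**Working it through.** **1. The plan's own dropout allowance.** The sample size section uses an arcsine formula with rates of 0.80 and 0.378, two-sided alpha 0.05 and beta 0.10. With λ = 12.654 (chi-square, 2 df, three groups) and an arcsine difference of 0.88999:

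n = 2 × 12.654 / 0.88999² = 31.95, so 32 per group and 96 in all.

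96 × 1.09 = 104.6, so 105. The stated figures reproduce. The allowance is 105 − 96 = 9 dropouts, or 3 per arm of 35 (3/35 = 8.6%).

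**2. Passages side by side.**

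| Item | What the article states |
|---|---|
| Who is a dropout | Includes patients who only stopped, missed or added treatment |
| What to pursue afterwards | Last laboratory test, conclusion form, reason |
| Laboratory outcomes named | Substance P, beta-endorphin (secondary) |
| Primary outcome | Change in VAS |
| VAS times in the text | Before and after treatment |
| Missing primary value | LOCF |

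If only the pre-treatment VAS exists for a dropout, LOCF carries baseline forward and the recorded change is 0.

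**3. Arm dependence.** Tablet counts can be applied only in groups B and C, and missed sessions only in A and C. Group C is exposed to both criteria.

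**4. Shift in one arm mean.** Shift = (patients misvalued / 35) × error per patient. The counts and millimetres are assumptions.

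- 3/35 × 30 mm = 2.6 mm
- 5/35 × 40 mm = 5.7 mm

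**5. False difference between two arms under baseline carry-forward.** Assume the same true mean change T in both arms, with dropouts who would have had that mean change. False difference = T × (difference in dropout shares).

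- Equal dropout (3 and 3 of 35): 0 mm for any T.
- Unequal dropout of 6 and 1 of 35, which with 2 in the third arm still totals the planned 9: (6 − 1)/35 × T = 4.3 mm at T = 30, 5.7 mm at T = 40 and 7.1 mm at T = 50. The arm with more dropouts looks worse.

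**6. How easily the session criterion is met.** If each of seven sessions is missed independently with probability m, the share of patients with at least one miss is 1 − (1 − m)⁷. This is 6.8% at m = 1%, 13.2% at 2% and 30.2% at 5%, against a planned 9–10% dropout for all reasons. Here m, independence and all seven sessions being due are assumptions. These are patients classed as dropouts, and not all would lack a VAS.

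**The case against.** The strongest reply is that the rule is silent on the VAS and does not exclude it. The article uses the word test loosely, even for the trial plan and the conclusion form, so the phrase may mean a final assessment. A stated purpose of efficacy and safety fits that better than two biomarkers do. The article condenses a full protocol, and the Fig. 3 schedule is not shown. The statistical section keeps dropouts in play through LOCF and a FAS.

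Much of this stands. Nothing shows that the VAS is in fact omitted, and LOCF means that what is lost is the observed endpoint, not necessarily the patient. Rescue steps are keyed to VAS, so interim readings may exist for some patients and would be carried forward instead of baseline, though the text does not make them scheduled outcome data. What does not stand is that this is mere omission. The article states a rule for data after dropout, gives its purpose, and names something other than the primary outcome.

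A reader might go further in three ways that the documents do not support.

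- *The case is closed once blood is drawn.* The text does not say so.
- *Postherpetic neuralgia will be known only in those who tolerated treatment.* The Follow-up section says "To evaluate the incidence of postherpetic neuralgia symptom, a follow-up call is designed and recorded 6 months later" and sets no such limit. The study design text speaks of the participants generally.
- *Failure of pain control makes a patient a dropout.* The Temporary analgesics section gives all three arms stepped rescue within the protocol. Only treatment outside the protocol counts as dropout.

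Patients who withdraw themselves or are lost may also be beyond reach, so the point applies mainly to the other categories.

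**Conclusion.** The point holds as a defect in a stated rule. Patients who stop or depart from treatment are classed as having left, and the instruction on what to secure for them does not name the primary outcome. With VAS described only before and after treatment, LOCF can turn this into recorded changes of zero, and arm-specific compliance criteria make the effect potentially unequal.

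The size is a few millimetres on a 100 mm scale: 2.6 to 5.7 mm in one arm mean, or about 4 to 7 mm as a false difference if the planned nine dropouts fall unevenly. It vanishes if dropout is equal and non-selective. These figures rest on assumed counts and VAS changes. The sample size is built on cure rates, so the article gives no expected VAS difference or standard deviation against which to judge them, and they do not show that a conclusion would change. The rule should be corrected because the missing values would be avoidable and could not be recovered later. It does not by itself invalidate the trial.

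**What to change.** In the two dropout sections:

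- Define discontinuation of study treatment separately from withdrawal of consent to data collection.
- Require the VAS and the Table 2 score at the common end-of-week time point for every randomised patient who has not withdrawn that consent, whatever treatment was received. Keep the blood sample as an addition.
- State that the 6-month postherpetic neuralgia call also applies to these patients.

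In the statistical section, use these observed values in the FAS wherever they exist, in place of carried-forward ones. Poor compliance and off-protocol treatment can then bear on the per-protocol set without ending data collection.

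Reconcile the missed-session criterion with the group A course description, which gives both seven daily treatments and an earlier end once pain has gone. It should be clear who is counted as non-compliant.

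None of the data-collection changes alters when treatment is given or stopped. The cost is a few sentences and a small effort to contact patients who stopped treatment.

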### Intervention

#### Group A

This group will be treated with only FC.
Acupoints: the main points are Ashi points (lesion area), corresponding nerve segment Jiaji points, and branch ditch points (SJ6); matching points are selected according to syndrome differentiation, pattern of dampness-heat in the liver meridian with Yang Ling Quan (GB34), pattern of dampness-heat in the spleen meridian with Yin Ling Quan (SP9), and pattern of obstruction of collaterals by blood stasis with blood sea (SP10).Appliances: medium-sized fire needle (diameter 0.4 mm), large-sized fire needle (diameter 0.65 mm), glass fire cup no. 1–5, medical cotton ball, alcohol lamp, lighter, iodophor, etc.Operational methods: routine disinfection of the skin with iodophor with the order of the head, middle, and tail of herpes will be carried out firstly. Holding 95% alcohol lamp by the left hand close to the needle, and to burn the needle in the right hand to whitening by the external flame of the fire, acupuncturist will prick the head of the herpes cluster. Then, the needles will be pricked into the blisters or rashes quickly from the surface of the skin to the base of the herpes. Pricking early-onset herpes at first, for larger pustules or blood blisters (diameter ε0.5 cm) with a large-scale fire, acupuncturist will extrude blister fluid with disinfection cotton ball after puncture, and then cup with a suitable size of glass fire cup for 5–10 min. If the area of the herpes cluster is too large, more than one cup can be used. The remaining acupuncture points are treated with fire needle pricking, and each acupuncture point should be pricked three times. Finally, the skin should be sterilized with iodophor more than one time. The treatment should be performed once a day for a total of 7 days.Skin care: after treatment, the iodophor is used to clean and disinfect the skin and to keep the patient’s skin dry and clean during the treatment.Course of treatment: the course of treatment is 1 week and from one to seven times. If there is no pain any more after one time of FC treatment, the course is just one time. Meanwhile, if the patient is still suffering pain, the FC will continue once a day unless the pain disappears. All the treatments will not be more than seven times no matter the pain or not.

#### Mechanism of fire needle cupping

Based on the theory of traditional Chinese medicine, the main causes of herpes zoster are dampness and heat, which could block the meridians and collaterals, and then led to the stagnation of blood and Qi, and finally, the pain is generated. FC has a strong effect to eliminate the dampness and heat, and make the Qi and blood smooth running, and then, the pain will be alleviated. Previous studies hint that FC can accelerate crusting and shedding of herpes, and also adjust the concentration of substance P in serum [11, 12].

#### Group B

Patients in group B are intervened with famciclovir plus gabapentin (FG). The famciclovir hydrochloride dosage is 0.25 g/time, 3 times a day according to the manufacturer’s (Livzon Pharmaceutical Factory) recommendation. The individual dose of gabapentin is 900–3600 mg per day. According to the manufacturer’s (Jiangsu Hengrui Pharmaceutical Co., Ltd.) recommendation (Table 1), the initial dose of 300 mg per day is gradually increased to 900 mg per day and then increased according to the patient’s needs, and the maximum dose is 3600 mg per day.

**Table 1 Tab1:** Gabapentin scheme

Day time	8:00 a.m.	14:00 p.m.	22:00 p.m.
1	–	–	300 mg
2	300 mg	–	300 mg
3	300 mg	300 mg	300 mg
Increase depending on patient’s needs			
4	300 mg	300 mg	600 mg
5	600 mg	300 mg	600 mg
6	600 mg	600 mg	600 mg
7 (maximum dose)	1200 mg	1200 mg	1200 mg

Table 1 demonstrates the gabapentin intake scheme used to reach the wanted therapeutic dosage.

#### Group C

In group C, patients will receive the treatment of FC plus famciclovir (FCF). The FC is performed the same as group A, and the usage and dosage of famciclovir hydrochloride are in line with group B.

#### Temporary analgesics

If the patients in the three groups still cannot endure the pain during the treatment or after 1 week treatment, and for all patients who have difficulties to endure pain during the trial, as an intra-trial arrangement, temporarily analgesic medicine will be given to those in need with careful observation. According to the recommendations of the World Health Organization, all three groups are likely to receive standardized analgesic treatment as follows: step 1—non-opioid analgesics (paracetamol 4·1.0 g), 60 mmδ VASδ 50 mm; step 2—moderate-strength opioids (tramadol tablets, maximum dose 600 mg/day), 80 mmδ VASδ 70 mm; step 3—moderate-strength opioids (tramadol injection, 0.1 g, once a day), VAS = 90 mm; and step 4—recommend the use of stronger opioids (dezocine injection, 5 mg, once a day), VAS = 100 mm. Patients are forbad to use other analgesic drugs or therapies. Temporary analgesic demand will be recorded (Table 2).

**Table 2 Tab2:** Secondary outcomes

**Symptom or sign (points)**	0	1		2		3	
Pain intensity	No	Mild		Medium, tolerable		Severe, unbearable	
Local itching	No	Mild		Medium, tolerable		Severe, unbearable	
Burning sensation	No	Mild		Medium, tolerable		Severe, unbearable	
Rash color	No	Light red		Red, no edema		Red, edema	
No. of blisters	No	1–10		11–15		> 26	
Blister clusters	No	1–2		3–4		4–5	
Ulcer	No	Epidermis		Superficial ulcer		Deep ulcer	
Fever	No	≤ 38 °C		≤ 39 °C		> 39 °C	
Local lymphadenopathy	No	< 0.5 cm		0.5–1 cm		> 1 cm	
Rash area reduction percentage	0	< 30%		< 60%		100%	
**Analgesic demand (day)**	**1**	**2**	**3**	**4**	**5**	**6**	**7**
Paracetamol (g)							
Tramadol (mg)							
Tramadol injection (g)							
Dezocineinjection (mg)							

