#### Secondary outcomes

First of all, pre- and post-treatment periods, the plasma of the participants is carefully collected and centrifuged and stored in a − 80 °C refrigerator. It is then the substance P and ®-Ep in serum can be detected by an enzyme-linked immunosorbent assay. Quantitative scoring methods have been further applied to evaluate the symptoms and physical signs before and after treatment, including pain intensity, local itching, burning sensation, rash color, numbers of blisters, clusters, ulcers, fever, local lymphadenopathy, and rash area (Table 2).

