#### Statistical analysis

The purpose of this study is to confirm whether the therapeutic effect of experimental therapy (fire needle cupping) is different from that of reference therapy (famciclovir plus gabapentin and fire needle cupping plus famciclovir). SPSS 20.0 statistical software will be used for data analysis. When the main efficacy indicators of individual subjects are missing, the last observation carried forward will be conducted, and the non-main efficacy indicators will not be carried forward. The mean ± standard deviation is used for statistical description of measurement data, and the frequency (constituent ratio) is used for statistical description of counting data. The baseline characteristics will be recorded as in Table 3. The group *t* test (Bonferroni method) will be used to compare the measurement data between groups. All reported *P* values will be two-tailed with 95% confidence intervals. The value of *P* ≤ 0.05 will be considered statistically significant. PPS analysis and Fas analysis will be performed at the same time. SS analysis is used for safety evaluation.

**Table 3 Tab3:** Baseline characteristics

Characteristics	Value
Age, mean ± SD, year	
Gender, *n* (%)	
Male	
Female	
Onset days, mean ± SD, days	
VAS score, mean ± SD	
Quantitative score, mean ± SD	

Onset days are the time from the patient’s onset of pain or rash to inclusion

Quantitative score is quantitative score of symptoms and signs

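### Table 2 of the protocol scores the rash area item, as labelled, in the opposite direction to the other nine items, and its blister, cluster and area bands leave gaps and an overlap

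*Protocol article*

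**What the plan says.** Under Secondary outcomes, the protocol article states: "Quantitative scoring methods have been further applied to evaluate the symptoms and physical signs before and after treatment". It lists ten items, the last named simply as rash area, and refers to Table 2 for the scoring.

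Table 2 (printed under Temporary analgesics) gives each item 0, 1, 2 or 3 points. For pain, itching and burning, 3 points means "Severe, unbearable"; rash colour, blisters, clusters, ulcer, fever and lymphadenopathy also start at none and rise with severity. Three rows matter here:

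| Item | 0 points | 1 point | 2 points | 3 points |
|---|---|---|---|---|
| "No. of blisters" | none | 1–10 | 11–15 | > 26 |
| "Blister clusters" | none | 1–2 | 3–4 | 4–5 |
| "Rash area reduction percentage" | 0 | < 30% | < 60% | 100% |

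Table 3 (Statistical analysis) lists one quantitative score, summarised by mean and SD, with the footnote "Quantitative score is quantitative score of symptoms and signs". Nothing elsewhere in the article reverses the area item, scores it apart from the others or corrects a band.

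**The concern.** A score built from several items needs every item to point the same way and every possible finding to fall in exactly one category. Table 2, as printed, meets neither condition.

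The area item measures improvement, while the other nine measure current severity. On its label, a patient whose rash clears gains points that mean worse disease everywhere else in the table. The item also cannot behave as a before-and-after measure: nothing has yet been reduced at baseline, so it can only stay level or rise.

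The band faults are independent of direction and of any summing. An assessor who finds 20 blisters, 4 clusters or an area value of 75% cannot apply the table without improvising, and two assessors may improvise differently.

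At stake is the only lesion scale the article gives. The Discussion says that skin lesion scores will receive close attention.

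**Working it through.** The plan states no figure for this score, so the check applies the bands as printed.

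**Bands.** Inputs are the three rows tabulated above.

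- Blisters: the second band ends at 15 and the third covers counts above 26. Unscored: 16 to 26, that is 26 − 16 + 1 = 11 counts. No overlap. If 15 is a misprint for 25, a count of 26 is still unscored.
- Clusters: 4 lies in both 3–4 (2 points) and 4–5 (3 points). Counts of 6 or more are unscored.
- Area: values from 60% to 99% are unscored, that is 99 − 60 + 1 = 40 whole percentages. Values above 0 and below 30% literally meet both < 30% and < 60%; that overlap disappears if the bands are read in sequence, and I do not count it as a fault.

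**Direction, if the ten items are summed.**

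- Range: 10 items × 3 points = 30.
- Fully healed patient, area row read as reduction: 9 × 0 + 3 = 3.
- Fully healed patient, area row read as area remaining: 9 × 0 + 0 = 0.

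**Change from baseline.** Let S be the baseline total on the other nine items, and take a patient who heals completely.

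- Read as reduction, with baseline entered as 0: the total goes from S to 3, a fall of S − 3.
- Read as area remaining, with baseline 100%: the total goes from S + 3 to 0, a fall of S + 3.
- The two readings differ by (S + 3) − (S − 3) = 6 points for the same patient.

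The inclusion criteria require rash, clustered blisters and pain. Taking at least 1 point each for pain, rash colour, blisters and clusters, S is at least 4. Even read as reduction, the total of a fully healed patient therefore falls by at least 4 − 3 = 1 point.

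**Between arms (illustration).** Assume that 60% of one arm and 20% of another clear fully. The documents give no such rates. Let patients who do not clear average m points on the area item in both arms. The better-healing arm is then charged (0.60 − 0.20) × (3 − m) extra points:

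| m | Extra points |
|---|---|
| 0 | 0.4 × 3 = 1.2 |
| 1 | 0.4 × 2 = 0.8 |
| 2 | 0.4 × 1 = 0.4 |

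Under these assumed rates the distortion is 0.4 to 1.2 points of 30. The upper end needs every patient who does not clear to score 0 on the item.

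**The case against.** The strongest reply is that the fault may lie in one word of a row label. Read as rash area remaining, the values 0, < 30%, < 60% and 100% run from best to worst like the other nine items, baseline is defined at 100%, and full recovery totals 0. Secondary outcomes calls the item rash area, with no mention of reduction. This is a plausible reading and it stands as an alternative. It does not remove the problem: the printed label says the opposite, and the 60 to 99% gap remains on either reading.

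A reader might infer that the score counts healing as worsening overall. The documents do not support that. One item of ten is affected; the other nine carry 27 of 30 points and fall as the patient recovers.

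Summing is also not stated. It is inferred from the single mean and SD in Table 3. The figure of 3 out of 30 depends on that inference; the band faults do not.

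Two further inferences go beyond the text. The article gives no distribution of blister counts, clusters or areas, so it cannot be said that the unscored values are common. Nor is there a basis here for adding that assessors are effectively unblinded: the Blinding section plans for outcome evaluators who do not know the grouping.

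The printed table is not excused by an unseen analysis plan or by PDF extraction. The scale is given in full, and the row values sit in ordered columns like those of the neighbouring rows.

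**Conclusion.** The point holds as a moderate fault in a secondary outcome. The area row, as labelled, contradicts the direction of the other nine items and cannot serve as a baseline measure. Whether the points or the label are wrong cannot be settled from the article.

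If the label is followed and the items are summed, full recovery scores 3 of 30 rather than 0, and differences between arms are diluted or distorted. A reversed comparison is possible in principle but is not shown.

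The gaps (11 blister counts, clusters above 5, area values of 60 to 99%) and the double category at 4 clusters follow directly from the table and need no assumption. How many patients they affect is unknown.

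The primary outcome is the VAS, and the sample size rests on cure rates of 37.8% and 80.0%; neither uses this score.

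**What to change.** 1. Define the area item so that higher means worse: either as rash area remaining relative to baseline, or as percentage reduction with the points reversed. Alternatively, take it out of the score and analyse percentage reduction separately. Settle label and direction in the same edit.
2. Make the bands contiguous, exclusive and exhaustive. Examples are blisters 1–10, 11–25 and > 25, and clusters 1–2, 3–4 and ≥ 5, with the area bands covering 60 to 99%. The exact cut-points are for the sponsor to confirm.
3. State whether the ten items are summed and, if so, give the range.
4. Record raw blister and cluster counts and measured areas on the case report form, and derive the points from them.
5. Rescore completed forms where raw values exist. The recruitment section dates the first formal recruitment to November 2018, whereas Trial status gives 10 October 2019, so some forms may already be filled in.

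The cost is an edit to one table and the matching form. Rescoring is straightforward only if raw values were kept, which the article does not say. Where only categories were recorded, patients in the gaps may not be recoverable.
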